##### Exclusion criteria

1. Babies without encephalopathy.
2. Babies with moderate or severe encephalopathy who meets the original NIHCD or the TOBY trial cooling trial criteria.
3. Babies with definite or probable seizures as per the recent ILAE classification.
4. Babies with moderate or severe abnormalities on aEEG voltage criteria.
5. Babies with life threatening congenital malformations.

**Cohort 2:** A total of 80 babies with mild encephalopathy ( $\geq 36$  weeks;  $\geq 2$ kg) aged 24 to 48 hours and undergoing cooling therapy as a part of clinical care of the recruiting centre will be recruited from several UK cooling centres, over a 2 year period. If the baby is eligible, parents will be approached for

recruitment between 24 to 48 hours after birth. The site investigator will review the baby's progress and aEEG over the first 24 hours, perform an NICHD neurological exam and will randomise the baby to rewarming after 48 hours or 72 hours of cooling therapy, if the baby meets the eligibility criteria. The chief investigator at Imperial College London will review the clinical and aEEG data if there is a dilemma about the trial eligibility.

Once the baby is recruited, MR imaging and spectroscopy will be performed between 4 to 14 days after birth, as in cohort 1. The babies recruited to cohort 1 will not be eligible for recruitment to cohort 2.

#### Inclusion criteria

1. Cooling therapy initiated within six hours of birth and continued beyond 24 hours by the clinical team on a baby who do not meet the original NICHD neonatal research network or the TOBY Trial Cooling criteria.
2. Evidence of acute perinatal asphyxia
  - a. Metabolic acidosis (pH <7.0 and/or BE >-16) in cord gas or a blood gas within one hour of birth.
  - OR
  - b. If the pH or BE is borderline (pH <7.15 to 7.0) and/or BE >-10 to -16) in cord and/or blood gas within 1h of birth, or no blood gas available, additional evidence of perinatal asphyxia is required, which includes either an acute obstetric event (e.g. cord prolapse, abruption, shoulder dystocia) OR Need for continued resuscitation or ventilation at 10 minutes and/or a 10 min Apgar score <6.

#### Exclusion criteria

- Babies with moderate or severe encephalopathy who meets the original NICHD or the TOBY trial cooling trial criteria.
- Babies with definite or probable seizures as per the recent ILAE classification at any stage until randomisation.
- Babies with moderate or severe abnormalities on aEEG voltage criteria at any stage until randomisation.
- Babies with life threatening congenital malformations

### **4.3 Study procedures**

Cohort 1: After informed parental consent a total of 60 babies with mild encephalopathy aged less than six hours will be randomised to usual care or whole-body cooling (rectal temperature  $33.5^{\circ}\text{C} \pm 0.5^{\circ}\text{C}$ ) for 72 hours. The babies in the usual care arm will have skin temperature monitoring instead of rectal temperature.

Cohort 2: The babies who are being cooled for encephalopathy without meeting the original cooling criteria (i.e. having a normal aEEG and/or a clinical examination consistent with mild encephalopathy) will be recruited between 24 to 48 hours of age. The babies will be randomised to rewarming at 48 hours or at 72 hours, at a rate of 0.5 C per hour.

Randomisation (web-based) will be performed at the cooling centre for all babies. The standard clinical referral pathway will be followed for out-born babies with mild NE, and the clinical assessment and randomisation will happen only at the cooling centre. However, the transport teams will provide the information leaflets and discuss the study with the parents prior to retrieval, so that the babies can be randomised immediately on admission.

Supportive treatment will be the same for all groups, as per the unit protocol. All babies will have amplitude integrated EEG within six hours of birth, for a minimum period of 24 hours, as part of standard clinical care. Following completion of cooling therapy, babies in the cooling arm will be rewarmed at a rate of 0.5°C per hour to eventually reach normothermia.

#### Use of sedation during cooling

Although sedation is often used during cooling in the UK, there is little evidence based to support this. In a non-randomised study, Thoresen et al. (2001) compared the brain injury in 18 piglets kept normothermic (39°C) with 21 piglets who were cooled to 35°C for 24 hours. The piglets were not given general anaesthesia, and no difference in brain injury was seen. The cooled piglets shivered and had elevated cortisol levels. The lack of neuroprotection was attributed to stress, possibly due to inadequate sedation, although the study examined anaesthetics rather than sedatives. Unlike piglets, newborn babies have brown fat and hence non-shivering thermogenesis occurs in response to cooling. Thus, the clinical implications of these data are unclear.

Furthermore, neuroprotection is observed in other animal models without sedation. More recent data from the sub-analysis of the NICHD cooling trial suggest that sedation had no effect on the neurodevelopmental outcomes. Secondary analysis of the MARBLE study shows routine pre-emptive opioid sedation prolongs hospital stay and increases hypotension, without any beneficial effects on neuroprotection or later neurodevelopmental outcomes. Hence, routine sedation will not be mandated in the COMET trial, and babies would be extubated whenever clinically stable.

#### Babies developing seizures after randomisation

A small number of babies (less than 5% in the PRIME study and MARBLE study) with mild encephalopathy during the initial assessment, may develop seizures and progress to moderate encephalopathy.

Recent evidence from delayed cooling trial suggests possibility of some neuroprotection even up to 24 hours of age. Hence, any baby developing seizures or progressing to moderate encephalopathy will receive cooling therapy for at least 72 hours as per the unit protocol. The data from these babies will be analysed as per the original allocation (Intention to treat).

#### aEEG and ECG

All babies will have aEEG as a part of the routine clinical care for the first 24 hours. In addition, 2 channel ECG data from the first 24 hours will be stored on a small portable device for analysis of heart rate variability.

#### Blood samples

We will collect 1 ml of blood at the time of randomisation and again at 80 hours from randomisation from all recruited babies. The blood (venous or arterial) will be collected, at the time of routine clinical sampling, whenever possible.

#### MR imaging and spectroscopy

All recruited babies will have 3 Tesla MR imaging and spectroscopy acquired between 4 and 7 days of age (prior to hospital discharge whenever possible). In addition to conventional T1 and T2, and diffusion tensor imaging, a series of spectroscopy data will be acquired in a 15x15x15mm^3 voxel centred on the thalamus to quantify NAA concentration. Due to the variance arising from inter-site scanner differences, an MR spectroscopy phantom will be used for calibration across all sites prior to starting the study. In the absence of a comprehensive diffusion phantom, inter-site diffusion data will be corrected post-hoc using ComBat. The results of the MR scans including any incidental findings will be fed back to the clinical teams for appropriate counselling of the parents.

#### 4.4 Withdrawal criteria

Withdrawal should occur only upon parental or clinician request. Recent data from the NICHD delayed cooling trial suggests potential benefits of cooling therapy for up to 24 hours of age in babies with moderate or severe encephalopathy. Hence, any baby who develops documented seizures (clinical and/or aEEG) between the age of 6 to 24 hours (i.e. after randomisation) will be considered to have moderate or severe encephalopathy, and will receive full cooling therapy for at least 72 hours, at the discretion of attending clinical teams. These babies will not be excluded from the study, and will be analysed in the originally allocated group (intention to treat).

#### 4.5. Diagnosis of neonatal seizures

Clinical diagnosis can miss almost half of the seizures in neonatal encephalopathy. Conversely, normal mannerisms may be misclassified as seizures if EEG is not used. Hence, the recent classification of neonatal seizures by the International league against epilepsy (ILAE) mandates the use of EEG or aEEG in neonatal intensive care units. Neonatal seizures are classified based on 5 levels of diagnostic certainty.

Level 1 (Definite seizures) – Seizures confirmed on conventional EEG with (electro-clinical seizure) or without (electro-graphic only) clinical manifestations.

Level 2a (Probable seizures) – Seizures confirmed on aEEG with (electro-clinical seizure) or without clinical manifestations (electro-graphic only)

Level 2b (Probable seizures) – Clinically assessed focal clonic or focal tonic seizure directly witnessed or reviewed on video by experienced medical personnel when EEG or aEEG was not available.

Level 3: (Possible seizure) – Clinical events suggestive of epileptic seizures other than focal clonic or focal tonic seizures, directly witnessed or reviewed on video by experienced medical personnel

Level 4: (Not seizure) – Reported seizure event (as previously defined) but insufficient evidence to meet the case definition

Level 5: (Not seizure) – Reported seizure event (as previously defined), documented or witnessed by experienced medical personnel and evaluated by simultaneous conventional EEG or aEEG and determined NOT to be a case of neonatal seizure.

#### 4.6 Outcome measures

- Mean thalamic [NAA] levels.
- Mean thalamic NAA/Choline and Creatine peak area metabolite ratios.
- Brain injury score on conventional MR imaging.
- Mean hospital stay.

#### 5. ADVERSE EVENTS

All known adverse events relating to neonatal encephalopathy and whole-body cooling are described in the parent information leaflet and will be discussed at the point of obtaining the informed research consent, prior to the start of cooling. The following clinical events occur due to the underlying disease (neonatal encephalopathy) although these are less likely in babies with mild neonatal encephalopathy. Previous data from cooling trials on babies with moderate and severe encephalopathy suggest that these adverse outcomes are reduced by cooling.

1. Brain injury on magnetic resonance imaging
2. Death during the neonatal period or during infancy
3. Adverse neurodevelopmental outcome at 18 months and at childhood
4. Persistent pulmonary hypertension
5. Metabolic imbalances

6. Cardiac arrhythmia
7. Thrombocytopenia
8. Renal failure
9. Coagulopathy

Whole-body cooling may increase the risk of the following adverse events.

1. Thrombocytopenia and an increased need for platelet transfusions
2. Subcutaneous fat necrosis

All adverse events are expected to occur within the cooling period (first 72 hours) or within 72 hours of re-warming. Adverse reactions occurring subsequently (after 1 week of life), except subcutaneous fat necrosis, will not be considered as relating to the intervention. Subcutaneous fat necrosis may occur several weeks after the intervention.

Serious adverse events that may be due to hypothermia are:

- Cardiac arrhythmia.
- Life-threatening bleeds
- Major venous thrombosis not related to an infusion line

## 6.1 DEFINITIONS

Adverse Event (AE): any untoward medical occurrence in a patient or clinical study subject.

Serious Adverse Event (SAE): any untoward and unexpected medical occurrence or effect that:

- Results in death
- Is life-threatening – refers to an event in which the subject was at risk of death at the time of the event; it does not refer to an event which hypothetically might have caused death if it were more severe
- Requires hospitalisation, or prolongation of a current inpatient's hospitalisation
- Results in persistent or significant disability or incapacity
- Is a congenital anomaly or birth defect

Medical judgement should be exercised in deciding whether an AE is serious in other situations, or performed by a delegated person according to the study delegation log. Important AEs that are not immediately life-threatening or do not result in death or hospitalisation (but may jeopardise the subject or require intervention to prevent one of the other outcomes listed in the definition above), should also be considered serious.

## 6.2 REPORTING PROCEDURES

All adverse events will be recorded during hospitalisation using the case report form. Babies who suffer neonatal encephalopathy are expected to have higher mortality and morbidity up to two years of age. If an UNEXPECTED serious adverse event occurs (i.e. an event not mentioned in the above list in 6.), it should be reported to the COMET trial manager at the Centre for Perinatal Neuroscience (CPN) at Imperial College London within 24 hours, using one of the Serious Adverse Event report forms. The COMET trial manager will ensure that the COMET Independent Data Monitoring Committee and the Research Ethics Committee are informed accordingly.

The Chief Investigator must notify the Sponsor of all unexpected SAEs. If there is any unexpected SAE which would be considered study related, the Chief Investigator will report to the Ethics Committee within 15 days of becoming aware of the event, using the SAE form. Local investigators should report any SAEs as required by their Sponsor and/or Research & Development Office.

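### Sections 5, 6.1 and 6.2 of the protocol disagree on what an SAE is and which SAEs reach the IDMC, and the stated AE recording period does not cover late fat necrosis

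*Protocol*

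**What the plan says.** **Definition.** Section 6.1 opens its definition of an SAE as "any untoward and unexpected medical occurrence or effect that" meets one of the usual seriousness criteria. A closing clause lets other events count as serious on medical judgement ("Important AEs that are not immediately life-threatening or do not result in death or hospitalisation") and does not ask that these be unexpected.

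**Lists.** Section 5 holds three lists: nine numbered events attributed to the disease, two numbered events that cooling may increase, and three bullets. The first list includes "Death during the neonatal period or during infancy" and cardiac arrhythmia. The second includes subcutaneous fat necrosis. The bullets are introduced by "Serious adverse events that may be due to hypothermia are" and name cardiac arrhythmia, life-threatening bleeds and major venous thrombosis unrelated to a line.

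**Reporting.** Section 6.2 sets the 24-hour rule: "If an UNEXPECTED serious adverse event occurs (i.e. an event not mentioned in the above list in 6.), it should be reported" to the trial manager, who passes it to the IDMC and the ethics committee. The chief investigator's duty to notify the sponsor also covers unexpected SAEs only. Local investigators report any SAE as their sponsor or R&D office requires.

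**Recording period.** Section 6.2 states that "All adverse events will be recorded during hospitalisation using the case report form". Section 5 states that "Subcutaneous fat necrosis may occur several weeks after the intervention".

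**The concern.** Seriousness and expectedness are separate properties. Seriousness decides what is collected and shown to a monitoring committee; expectedness decides what is expedited to outside bodies. Section 6.1 merges the two, and section 6.2 then uses expectedness to decide what the IDMC is told.

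This matters because section 2 says that the safety of cooling in mild encephalopathy is unknown, and cohort 1 randomises babies to cooling or no cooling. Deaths and serious events that cooling might cause are what an IDMC needs by arm. A list meant to record what is anticipated should not be what removes them from the only stated notification. Because the pointer to that list does not resolve, sites can also apply the rule differently in good faith.

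The second strand is narrower. Fat necrosis is one of only two events that section 5 says cooling may increase, and it can appear after the period in which AEs are said to be recorded.

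**Working it through.** No figure in the protocol bears on this point, so the check sets the passages side by side.

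**1. Definition against use.** Under section 6.1, an SAE must be unexpected. Section 5 names three SAEs that are anticipated under hypothermia, which that definition would not allow. Section 6.2 speaks of an unexpected SAE, which presupposes that expected SAEs exist. The definition therefore conflicts with both neighbouring sections. The closing clause of section 6.1 does not repair this. It concerns events short of death or immediate threat to life, so it does not bring an expected death back in.

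**2. The list reference.** Section 6.2 points upward to a list under 6. In the index and in the body, heading 6 is assessment and follow-up, which comes after section 6.2. The event lists are under heading 5, and there are three of them, while the reference is singular.

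**3. What each reading exempts from the 24-hour and IDMC route.**

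| Reading of the list | Death | Cardiac arrhythmia | Life-threatening bleed | Major venous thrombosis |
|---|---|---|---|---|
| First or both numbered lists in section 5 | exempt | exempt | reportable | reportable |
| All three lists in section 5 | exempt | exempt | exempt | exempt |
| Bulleted list in section 5 only | reportable | exempt | exempt | exempt |
| Seriousness criteria in section 6.1 | exempt | exempt | exempt | exempt |

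The last row can be set aside: it would exempt every event that meets a seriousness criterion and leave almost nothing to report. The third row is possible, because the reference is singular. It fits poorly with section 6.2, which says just before the rule that higher mortality up to two years is expected in these babies. Taking the reference to mean the section 5 lists, death and cardiac arrhythmia are exempt, and the other two events depend on whether the bullets count.

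**4. Other routes.** The IDMC is named only in section 6.2, as the consequence of an unexpected SAE report. Section 9 makes the Project Management Group responsible for collecting AE data but does not describe passing them on. The sentence on local investigators covers any SAE but leads to the local sponsor or R&D office.

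**5. Recording period.** Section 5 expects AEs during cooling or within 72 hours of rewarming. It treats reactions after one week of life as unrelated, with fat necrosis as the one exception. The hospital-stay window therefore conflicts with section 5 for fat necrosis only. Death and disability are collected later, at 18 to 24 months (section 7.1), but fat necrosis is not among those outcomes.

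**The case against.** The best defence is that section 6.2 sets an expedited route and nothing more. AEs in hospital go on the CRF, AE data are collected centrally, an IDMC exists, and what it sees at its reviews is commonly set in a charter. The charter is not shown. **This stands.** A reader might infer that deaths and hypothermia SAEs are withheld from the IDMC. The protocol does not say so: silence about periodic review is not a bar to it.

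Other stronger inferences also go beyond the text:

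- *Expected deaths are not SAEs in this trial.* The definition read alone says this, but sections 5 and 6.2 use the term otherwise. It is a contradiction, not a settled operating rule.
- *All four named events are exempt.* For bleeds and thrombosis, this holds only if the bullets are part of the list.
- *The list was drawn from moderate or severe disease.* Section 5 attributes the events to neonatal encephalopathy and calls them less likely in mild cases. The moderate and severe data are cited for a different statement, that cooling reduces them.
- *Safety capture ends at discharge.* AE recording is stated only for the hospital stay, but the SAE rule has no stated end date, and death and disability are collected at 18 to 24 months.
- *Unequal hospital stay biases AE comparisons.* Length of stay is itself compared between arms, so unequal observation is possible, but nothing shows that it will occur or matter.
- *Small arms make the defect measurable.* Assuming 30 babies per arm in cohort 1, zero events leave a one-sided 95% upper bound of 1 − 0.05^(1/30) = 9.5%. The arithmetic is right, but it applies to any arm of 30 and does not measure this defect.

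The charter argument does not rescue the wording. The protocol is what sites follow, and its definition and list reference are wrong on the page whatever a charter says.

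**Conclusion.** The three safety sections contradict each other and need to be reconciled. The SAE definition conflicts with the anticipated SAEs in section 5 and with the wording of section 6.2. The only stated IDMC notification rests on a list reference that does not resolve. Read as the section 5 lists, two of the four named serious events (death, cardiac arrhythmia) fall outside that route, and all four do if the bulleted list is included. Separately, one harm that the protocol links to cooling, fat necrosis, can arise after the stated AE recording period.

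This rests on the protocol alone and on taking the reference to mean section 5. If a charter gives the IDMC all deaths and SAEs by arm, the practical gap shrinks to timing and to inconsistent reporting by sites; the contradictions in the text remain. The finding is about the rule as written. It does not show that any event has been or will be missed.

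**What to change.** 1. In section 6.1, delete *and unexpected* from the SAE definition.
2. Define expectedness separately, against one correctly numbered list, and say which of the section 5 lists belong to it.
3. In section 6.2, state that all deaths and all listed SAEs, including those named as possibly due to hypothermia, go to the trial manager and reach the IDMC by arm. Keep expectedness only as the criterion for the expedited ethics report. If a charter already sets periodic review, refer to it.
4. Set one AE collection window, ending at the same age in every arm, that covers late fat necrosis. A CRF item at an existing post-discharge contact would do. The only such contacts the protocol describes are the 18 to 24 month assessment and the two-year questionnaire, so an earlier routine contact, where sites have one, would rely less on recall.

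The cost is protocol wording, a few more SAE forms and one CRF item across 140 babies.

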## **6. ASSESSMENT AND FOLLOW-UP**

### **7.1 Neurodevelopmental evaluation**

All babies will have detailed neurodevelopmental evaluation including Bayley Scales of Infant Development (BSID-III or IV if available), Gross Motor Function Classification System (GMFCS), and hearing and vision assessment between 18 to 24 months of age. Severe disability will be defined as any one of the following: both cognitive and language composite BSID-III scores <70, GMFCS level 3–5, hearing impairment requiring hearing aids, or blindness. Moderate disability will be defined as both cognitive and language composite BSID-III scores between 70 and 84 and one or more of the following: GMFCS level 2, hearing impairment with no need for amplification or a persistent seizure disorder. The outcomes will also be assessed by categorisation of these scores and by including mortality as an outcome. An adverse outcome will be defined as death or, in survivors, moderate or severe disability.

We will also send parents an adapted Parent Report of Children's Abilities – Revised (PARCA- R) at 2 years of age. It is a parent completed questionnaire that can be used to assess children's cognitive and language development. This tool will be sent to parents from both cohorts (HIE and Healthy) to obtain reference values for the questionnaire. This is important to ensure the study gathers long term follow-up data for all participants, regardless of clinical practice as well as capturing developmental difficulties that may be perceived by parents but not detected in BSID-III. PARCA has been validated to measure cognitive abilities and behavioural adjustment and is available non commercially.

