### Brain injury and outcomes after mild encephalopathy

50% of affected babies with mild encephalopathy have brain injury on magnetic resonance (MR) imaging, and one third are reported to have an adverse long term neurodevelopmental outcome. Jacobs et al. (2011) reported adverse neurodevelopmental outcomes at two years of age in 8/24 (33%) children who had mild NE at birth and were not cooled. Murray et al. (2016) reported significantly lower full scale IQ, verbal IQ and performance IQ in 22 children following mild NE, when compared with 30 healthy controls, assessed at five years of age ( $p < 0.005$ ). Lally et al. (2014) have reported neurodevelopmental delays at 3.5 years of age in 8/24 (33%) south Indian babies with mild NE. Such neurodevelopmental impairments will have a profound lifelong impact, including an increased risk of autism^17, attention deficit disorders and learning difficulties.

The most accurate data on later outcomes after un-treated mild encephalopathy comes from the multicentre PRIME (Prospective research in mild encephalopathy) study. The PRIME study reported adverse neurodevelopmental outcomes at 2 years in 16% of babies with un-treated mild neonatal encephalopathy. Of these approximately 40% had severe adverse outcomes (Bayley III cognitive composite score  $< 70$ ; Gross motor function classification (GMFCS): 3 to 5) and 60% had mild adverse outcomes (Bayley III cognitive 70–84 or  $\geq 85$  and either GMFCS 1 or 2, seizures, or hearing deficit).

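### The disability definition at 18 to 24 months is not monotone: a child with exactly one Bayley composite below 70 can be classed as free of adverse outcome while a better-scoring child is classed as moderately disabled

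*Protocol*

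**What the plan says.** Protocol section 7.1 defines severe disability as any one of: "both cognitive and language composite BSID-III scores <70, GMFCS level 3–5, hearing impairment requiring hearing aids, or blindness". The next sentence reads "Moderate disability will be defined as both cognitive and language composite BSID-III scores between 70 and 84 and one or more of the following", and the list is "GMFCS level 2, hearing impairment with no need for amplification or a persistent seizure disorder". The binary endpoint follows: "An adverse outcome will be defined as death or, in survivors, moderate or severe disability".

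The section adds that "The outcomes will also be assessed by categorisation of these scores and by including mortality as an outcome", but gives no rule for a child whose two composites fall in different bands.

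The assessment is planned for all babies in both cohorts (60 + 80 = 140). It is not among the primary or secondary aims in section 3 or the outcome measures in section 4.6. The primary outcome is thalamic NAA.

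**The concern.** Both score conditions require the two composites to sit in the same band. Once one composite drops below 70 and the other does not, the child leaves the moderate band without entering the severe one. Nothing catches the child except the stand-alone routes to severe disability (GMFCS level 3 to 5, hearing aids, blindness).

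An ordered outcome must never improve when a child gets worse and all else stays fixed. This one can. At stake is the only clinical adverse outcome that the protocol defines. Its rate would be too low, and some children with poorer scores would be counted among the good outcomes.

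**Working it through.** **Step 1: apply the rule as written.** The inputs are the two definitions in section 7.1. The table covers every pair of bands for a child with no stand-alone route to severe disability. In the last column the child has GMFCS level 2, unaided hearing loss and a persistent seizure disorder.

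| Cognitive | Language | No other deficit | All three listed deficits |
|---|---|---|---|
| <70 | <70 | severe | severe |
| <70 | 70–84 | none | none |
| <70 | ≥85 | none | none |
| 70–84 | <70 | none | none |
| 70–84 | 70–84 | none | moderate |
| 70–84 | ≥85 | none | none |
| ≥85 | <70 | none | none |
| ≥85 | 70–84 | none | none |
| ≥85 | ≥85 | none | none |

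In all four pairs with exactly one composite below 70 the child is in neither class, whatever listed deficits are added.

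**Step 2: show the inversion.**
- Child A: cognitive 75, language 75, GMFCS level 2. Moderate, so adverse.
- Child B: cognitive 60, language 75, GMFCS level 2, persistent seizures. Neither class, so not adverse.

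B is no better than A on any item and worse on two, yet gets the better class. This step needs no distributional assumption.

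**Step 3: illustrate the size.** The protocol states no figure to reproduce and gives no mean, SD or correlation for the composites. Assumed: bivariate normal, common mean μ of 90 to 100, SD 15, correlation ρ of 0.5 to 0.8.

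- One given composite below 70: p = Φ((70 − μ)/15)
- Both below 70: b = Φ₂(z, z; ρ), with z = (70 − μ)/15
- At least one below 70: 2p − b
- Exactly one below 70: 2(p − b)

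| μ | ρ | At least one <70 | Both <70 | Exactly one <70 | Of 140 babies |
|---|---|---|---|---|---|
| 100 | 0.8 | 3.57% | 0.98% | 2.59% | 3.6 |
| 95 | 0.7 | 7.71% | 1.85% | 5.85% | 8.2 |
| 90 | 0.5 | 15.40% | 2.84% | 12.55% | 17.6 |

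(Percentages come from unrounded values.) The first and last rows are the extremes of the grid, so the range is about 4 to 18 babies, with about 8 in the middle case. As a share of children with any composite below 70, 62% to 90% miss the severe score route across the grid (76% in the middle case). That share is of a small group, so the count is the fairer measure.

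**Step 4: direction.** Suppose the bands were set on the lower composite, or on the cognitive composite alone. Every child now adverse would stay adverse: both below 70 remains severe, and both in 70–84 with a deficit remains moderate. Either repair only adds children, so against either one the written rule understates. The amount depends on the repair. With the cognitive composite alone, the middle case gives p − b = 4.78% − 1.85% = 2.93%, about 4 of 140 with a cognitive score below 70 but not both.

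**The case against.** The strongest reply is about weight. The endpoint is outside the aims and the outcome list, the sample sizes of 60 and 80 are not tied to it, and the rule is the same in both arms. Both composites are collected, so nothing is lost for good, and the planned categorisation of scores may show single low scores separately. All of that stands and lowers the priority. It does not repair the binary rule.

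It is also fair that the counts rest on assumed parameters, that children severe through GMFCS, hearing or vision are not subtracted, and that the binary outcome does give every child one value. Strict inversion, as in Step 2, needs one composite below 70, the other in 70–84, and a listed deficit. The protocol gives no frequency for that combination, so 4 to 18 counts children who miss the score route, not inverted pairs.

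A reader might infer two stronger things. The first is that the rule breaks comparison with the background figure: "The PRIME study reported adverse neurodevelopmental outcomes at 2 years in 16% of babies with un-treated mild neonatal encephalopathy". The documents do not support this as a consequence of the word both. The PRIME outcome described there is not the cognitive score alone: its severe class also includes GMFCS 3 to 5, and its mild class uses GMFCS 1 or 2, seizures or hearing deficit. About 60% of the 16% (0.60 × 16% = 9.6 percentage points) were mild outcomes, whereas this trial counts death or moderate or severe disability. The rates would differ under either repair, and the protocol nowhere says that it will benchmark against 16%.

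The second is that a later clinical-outcome trial would be planned from this rate. No such trial is announced, and the protocol's illustrative phase III calculation uses a 20% control rate.

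**Conclusion.** Wrong as written, and a should-fix. That a child with one composite below 70 can be ranked above a better-scoring child follows from the text alone. The number of babies with exactly one composite below 70, about 4 to 18 of 140 with about 8 at mean 95 and correlation 0.7, depends on the assumed bivariate normal model. It is an upper figure for those affected through this gap, because children severe by another route, deaths and losses to follow-up are not removed. The primary NAA analysis and the sample sizes do not change.

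**What to change.** Before any 18 to 24 month outcome is classified, reword the two definition sentences in section 7.1 so that:
- every pair of cognitive and language composites, with the listed deficits, leads to exactly one class; and
- a lower score, or an added deficit, never moves a child to a better class.

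Two ways to do this are to band on the lower of the two composites, or to band on one composite named in advance. They differ in stringency, and the sponsor should choose and record the choice. Whether a child with both scores in 70–84 and no further deficit should count as moderate is also a matter of stringency; the present answer does not break the ordering.

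The cost is two sentences in a protocol amendment. No new data are needed, because both composites come from the planned assessment. Making the change before classification keeps the choice from being influenced by the results.
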